### Interim analyses {21b}

The PI will have access to interim results and make the final decision to terminate the trial.

### Methods for additional analyses (e.g., subgroup analyses) {20b}

Not applicable

### Methods in analysis to handle protocol nonadherence and any statistical methods to handle missing data {20c}

Randomized clinical trials analyzed using the intent-to-treat (ITT) approach provide unbiased comparisons between treatment groups. In cases of nonadherence, intent-to-treat analysis will be performed to avoid overlap and exclusion effects that could disrupt the random assignment of treatment groups in the study. The ITT analysis will provide information on the potential effects of treatment policies rather than on the potential effects of a particular treatment.

### Plans to give access to the full protocol, participant-level data, and statistical code {31c}

Not applicable.

## Oversight and monitoring

### Composition of the coordinating center and trial steering committee {5d}

The principal investigator (PI) is responsible for the overall project and for organizing steering committee meetings. An independent steering committee will be responsible for ensuring the overall safety of participants, coordinating study meetings, supervising the study, monitoring data safety, and overseeing the quality control.

### Composition of the data monitoring committee, its role, and reporting structure {21a}

The composition of the data monitoring committee (DMC) is not needed because the PI organizes an independent steering committee meeting.

### Adverse event reporting and harms {22}

An adverse event (AE) refers to any untoward event that occurs during the clinical study but that does not necessarily have a causal relationship with the surgical treatment. Safety evaluations are performed from the point at which the signature on the informed consent form is obtained until the end of the study or until the patient withdraws from the trial, according to the management requirements. AEs and serious adverse events (SAEs) will be reported.

An SAE is an event that causes hospitalization, prolonged hospitalization, disability, incapacity, life-threatening illness or death, or congenital malformation during the clinical trial.

During the study, all AEs will be recorded. These records include the type of AE (using standard medical terminology), the date of the AE, the date of the disappearance/stabilization of the AE, the severity of the AE, the impact of the AE on the surgery, the relationship of the AE with the surgery, the treatment measures, and the outcomes. If an SAE occurs, researchers fill out an SAE report form. The report is signed and dated and reported to the Ethics Committee of The Society of Bariatric and Metabolic Surgeons of Kazakhstan (Nur-Sultan, Kazakhstan) within 24 h.

### Frequency and plans for auditing trial conduct {23}

Frequency for auditing trial conduct: 12, 24, and 36 months after surgery.

The process will be independent from investigators and the sponsor.

### Plans for communicating important protocol amendments to relevant parties (e.g., trial participants, ethical committees) {25}

If the acceptance criteria, the results, and analyses are changed, this information will be communicated to all trial participants and to the ethics committee in writing (letters).

A sponsor will submit a protocol amendment in cases when there are changes in the existing protocol that significantly affect the safety of subjects, scope of the investigation, or scientific quality of the study.

### Dissemination plans {31a}

The trial results will be distributed in journal publications.

## Discussion

Advances in bariatric and metabolic surgery make it possible to include this subspecialty in our national health systems as an independent specialization [17]. LOAGB is recognized as a simple and safe gastric bypass method [12], and LOAGB has been shown to match RYGB in weight loss and metabolic improvement after 2 years [18].

However, the high likelihood of intractable biliary reflux in LOAGB, 2.8% after revisional bariatric procedures (r-LOAGB) and 0.4% after primary LOAGB (p-LOAGB), is a serious complication. A. Soprani et al. [19] collected a series of 16 patients who underwent laparoscopic Nissen/MGB for large sliding hiatal hernia or paraesophageal hernia between 2013 and 2016. The surgery consisted of a standard MGB combined with crural repair and Nissen fundoplication using the remnant stomach as an anti-reflux valve. During this period, ten patients underwent Nissen/MGB after laparoscopic adjustable gastric band (LAGB) (seven two-stage and three one-stage procedures). None of these patients developed postoperative symptomatic bile reflux.

Our current study, for the first time, investigates the results of applying a similar method for all cases of morbid obesity according to the specified inclusion criteria. Thus, regardless of the presence or absence of insufficiency of the lower esophageal sphincter and hiatal hernia, in the experimental group, we will perform a bariatric surgical procedure, which we called “FundoRingOAGB.” The combination of gastric bypass and fundoplication (CGB&F) as described in the publication can be classified into three main types:
Type 1 CGB&F—One-stage: simultaneous gastric bypass and fundoplication.Type 2 CGB&F—Two-stage: consequent gastric bypass after fundoplication with (a) complete takedown of the wrap; (b) partial takedown of the wrap; and (c) without takedown of the wrap.Type 3 CGB&F—Two-stage: sequential fundoplication after a previous bariatric surgery.Type 1 CGB&F includes primary bariatric procedures, and types 2–3 are secondary surgical procedures [13].

The return of weight after any gastric bypass method significantly reduces the preference for using bariatric and metabolic surgery for the treatment of morbid obesity; therefore, we first examined the likelihood of weight return after the experimental (FundoRingOAGB) and standard procedure of LOAGB. For the primary outcome measure, the change in body mass index will be assessed 12, 24, and 36 months after the surgical procedure.

Simultaneously, secondary outcome measures were the likelihood of biliary reflux within 12, 24, and 36 months after this procedure. Finally, GERD will be assessed if preoperative GERD symptoms are present or if GERD symptoms occur postoperatively (de novo GERD). For this aim, we will use a quality-of-life scale for gastroesophageal reflux disease (GERD-HRQL) [20].

In the present randomized controlled trial, we expect to show that one anastomosis gastric bypass with fundoplication ring for obese patients will better prevent the return of weight and bile reflux than the standard method. The idea to investigate in a randomized study the combination of two procedures as a primary procedure for one-anastomotic gastric bypass was expressed by [name] [13, 21].

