## Introduction

### Background and rationale {6a}

Typical early weight loss following bariatric surgery ranges from 47 to 80% of excess weight [1]. However, typical weight regain is 15–25% of that lost weight [2]. Weight regain after surgery is a major problem in bariatric practice. Therefore, adjustable bands and rings are used, such as “FobiRing” for banded gastric bypass [3]. However, foreign material can cause complications, such as erosion of the stomach wall [4]. Therefore, surgeons avoid the use of mechanical devices for banded gastric bypass.

Currently, laparoscopic one anastomosis gastric bypass (LOAGB) or minigastric bypass (MGB) is a common bariatric procedure for treating obesity [5]. The greatest criticism of the LOAGB is for the likelihood of biliary reflux [6]. Biliary reflux resistant to medical treatment has an incidence of 0.6–10% after one anastomosis gastric bypass and may be a reason for revisional surgery [7].

In addition, along with obesity, gastroesophageal reflux disease (GERD) is steadily increasing worldwide, and antireflux surgery must be performed simultaneously with bariatric surgery in obese patients [8]. In these cases, fundoplication may be performed using the fundus of the excluded part of the stomach [9]. Colpaert J et al. reported good short-term results with modified Nissen fundoplication for patients with reflux after RYGB [10]. They opted to perform the same procedure to slow down the passage of food through the gastric pouch. This procedure can be performed as a revision procedure after Roux-en-Y gastric bypass for the treatment of postoperative dumping syndrome [11].

In the literature, we did not find data on the use of a similar method for primary procedures and examples of use for patients without GERD to prevent biliary reflux in one anastomosis gastric bypass and de novo postoperative reflux esophagitis.

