### Sample size {14}

Purpose sampling
Effect size (*d*) (postoperative change in BMI (%)) = 15%.SD = 10.

Formula for calculating sample size is:
$$ n=2\ \left( Z\alpha +Z\left[1-\beta \right]\right)2\times \mathrm{SD}2/\mathrm{d}2 $$

Level of significance = 5%, power = 80% (Sample size increases as power increases. Higher the power, lower the chance of missing a real effect), *Zα* = *Z* is constant set by convention according to accepted α error and *Z* (1-*β*) = *Z* is constant set by convention according to the power of study [16].

Sample size calculations in our study:
$$ \mathrm{Z}\alpha =1.96,\mathrm{Z}\ \left(1-\beta \right)=1.28,\mathrm{SD}=10,\mathrm{d}\ \left(\mathrm{effect}\ \mathrm{size}\right)=15 $$

*n* = 2 (1.96 +   1.28) 2 × 102/152 = 9.33 individuals in each group should be recruited in the study. However, we plan to include more than five times the number of patients in the sample.

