### Recruitment {15}

We will sample a homogenous population group (obese patients with body mass index (BMI) from 30 to 50 kg/m^2^), thus reducing the standard deviation and hence the sample size. We will recruit 100 obese patients (50 patients in two groups).

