## Statistical methods

### Statistical methods for primary and secondary outcomes {20a}

Statistical analysis will be performed using Microsoft Excel for Mac (Microsoft Corp., Redmond, WA) and StatPlus: MacPro (AnalystSoft Inc., Walnut, CA).

The normal distribution of the variables will be tested using the Kolmogorov–Smirnov test. Subsequently, quantitative demographic and outcome variables will be reported as the means and standard deviations (SD); qualitative variables will be reported as counts and percentages. Between-group comparisons among quantitative variables will be performed using independent one-way ANOVA. Where ANOVA omnibus F test is significant, pairwise comparisons using Fisher's least significant difference (LSD) method will be performed. Between-group differences among qualitative variables will be assessed using the chi-square test or Fisher's exact probability test. Measures of within-group change in quantitative variables, from baseline out to 12, 24, and 36 months, will be analyzed using the dependent-samples *t* test. Correlation and linear regression analyses will be performed to assess the strength and direction of the relationship between changes in BMI and telomere length and to estimate the predictive value of BMI change relative to telomere length at the 12-, 24-, and 36-month follow-ups. Statistical significance was set at *p* < 0.05.

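### Bile reflux is graded on an ordered scale but assigned to tests that ignore order, and 50 patients per arm give little basis for a conclusion about intractable reflux alone

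*Protocol article*

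**What the plan says.** All references are to the protocol article.

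- **Endpoint.** Outcomes {12}, secondary outcome: bile reflux is assessed at 12, 24 and 36 months on three rising grades. Mild is asymptomatic and seen only at endoscopy. Average involves pain or gastritis of the whole pouch. Severe is intolerable symptoms, or esophagitis with bile in the esophagus. With no reflux as the lowest level, this is a four-level ordered scale.
- **Test.** Section {20a}: "Between-group differences among qualitative variables will be assessed using the chi-square test or Fisher's exact probability test". No other between-group method is named for a categorical outcome.
- **Rates.** Background {6a}: "Biliary reflux resistant to medical treatment has an incidence of 0.6–10% after one anastomosis gastric bypass". The Discussion gives intractable reflux as "2.8% after revisional bariatric procedures (r-LOAGB) and 0.4% after primary LOAGB (p-LOAGB". No rate is given for mild or average reflux, or for reflux of any grade.
- **Size.** Recruitment {15}: "We will recruit 100 obese patients (50 patients in two groups". The sample size rests on BMI change alone.
- **Expectation.** The Discussion expects to show that the wrap "will better prevent the return of weight and bile reflux than the standard method".

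**The concern.** Two things do not fit together.

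First, the endpoint carries order and the named tests do not use it. A chi-square or Fisher test on the four-level table would give the same p-value if the grades were shuffled. Used on reflux present or absent, it discards the difference between an asymptomatic endoscopic finding and intolerable symptoms. With 50 per arm that information is worth keeping.

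Second, the reflux that motivates the trial is the intractable or treatment-resistant form, and the rates quoted for it are mostly low. If the expected conclusion were read as covering that form, a non-significant result would say little about the wrap. At the lower quoted rates, a wrap arm without severe events would say little as well, although it could be mistaken for prevention.

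**Working it through.** **The plan's own figure.** Section {14} uses n = 2(Zα + Z(1−β))² × SD²/d² with 1.96, 1.28, SD 10 and d 15: 2 × 3.24² × 100/225 = 9.33 per group, as printed. (Z = 1.28 corresponds to 90% power, not the stated 80%. That is a separate matter and does not affect this point.) There is no corresponding figure for bile reflux to reproduce.

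**Part 1: ordered grade, 50 per arm, two-sided 5%.** The article gives no grade distribution, so three are assumed for controls. The wrap arm is obtained by multiplying the odds of being at or above each grade by 0.4. For the first row, the proportion with any reflux goes from 0.40 (odds 0.667) to odds 0.267, which is 0.211. Power by simulation:

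| Control none/mild/average/severe (assumed) | Wilcoxon rank-sum | Unordered chi-square |
|---|---|---|
| 60/25/10/5% | 57% | 38% |
| 50/25/15/10% | 63% | 43% |
| 70/15/10/5% | 46% | 29% |

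A repeat run with 20,000 simulated trials per row agreed to within about two percentage points, so the rank test lies at about 47–63% and the unordered table at about 29–43%. Fisher's test on any reflux against none gave about 38–53%. With the odds ratio set to 1, the rank test rejected in about 5% of runs, so its advantage is not bought with a raised error rate.

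**Part 2: intractable or treatment-resistant reflux, 50 per arm.** Take the best case for the wrap, 0 events in 50.

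1. Fisher two-sided p is 0.056 for 5/50 against 0/50 and 0.027 for 6/50 against 0/50. At least 6 control events are needed.
2. Power is then P(X ≥ 6) with X ~ Binomial(50, p):

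| Control rate p | Source | Expected control events, 50p | Power, Fisher | Chance of 0/50 if the wrap has no effect, (1−p)^50 |
|---|---|---|---|---|
| 0.4% | Discussion, primary surgery | 0.2 | 6 × 10⁻⁸ | 82% |
| 0.6% | Background, lower end | 0.3 | 6 × 10⁻⁷ | 74% |
| 5% | intermediate value, assumed | 2.5 | 3.8% | 8% |
| 10% | Background, upper end | 5 | 38% | 0.5% |

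3. An uncorrected chi-square needs only 4 control events (p = 0.041). Its power is 0.02% at 0.6%, 24% at 5% and 75% at 10%. At 10% with complete prevention, the 5 expected events spread over two arms give 2.5 per event cell, too few for that approximation to be trusted.
4. The exact two-sided 95% upper limit for 0/50 is 1 − 0.025^(1/50) = 7.1%, about 18 times the 0.4% rate (7.1/0.4).
5. Losses make this worse. With 40 evaluable per arm (an assumption, since no dropout rate is stated), power at 10% falls to 21%.

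**The case against.** **On the test.** Section {20a} is one general sentence for all qualitative variables. It does not say that bile reflux will be analysed as an unordered four-level table, and the coding could be settled in an analysis plan that is not shown. Chi-square and Fisher tests are valid here. This is fair: the point is one of efficiency, not validity. But the article does name a method, and whichever way it is applied, the order is lost. The grades also mix symptoms with endoscopic findings, so proportional odds cannot be taken for granted. That favours the rank test as the default.

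**On the rates.** Three stronger readings are tempting, and the article does not support them.

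- A reader might infer that clinically relevant reflux in general is too rare to study here. The quoted rates cover intractable or treatment-resistant reflux only. Average-grade reflux with pain also matters clinically and has no quoted rate. If any-grade reflux were 20% in controls (an assumption), complete prevention would have 95% Fisher power.
- A reader might infer that, because earlier stomach or esophageal surgery is excluded, controls must have the 0.4% rate. The Background range of 0.6–10% is not split by primary and revisional surgery and does not contain 0.4%. Patients with hiatal hernia or GERD symptoms can still be enrolled.
- A reader might infer that no events in the wrap arm is the expected result whether or not the wrap works. That holds at 0.4–0.6%, but at 5% and 10% an ineffective wrap would give 0/50 only 8% and 0.5% of the time.

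**On status.** Bile reflux is a secondary outcome, so the absence of a power calculation is not an error. The Discussion states an expectation, not a decision rule, and does not say that an absence of severe events will be read as prevention. This stands, and it reduces the second part to a limit on interpretation.

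**Conclusion.** The point holds in two parts of different weight.

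The main part is the analysis. An ordered secondary endpoint is assigned to tests that cannot use its order. The power given up is roughly 17 to 20 percentage points against the unordered table (46 − 29 = 17; 63 − 43 = 20), and about 10 points against present-or-absent Fisher (63 − 53 = 10). These figures rest on assumed grade distributions and a common odds ratio of 0.4. The direction was the same in all three distributions tried. Even the rank test stays below 80% power, so the change improves the comparison without guaranteeing an answer.

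The lesser part is a limit on the conclusion. For intractable or treatment-resistant reflux alone, complete prevention would usually not reach Fisher significance anywhere in the article's quoted range: near zero at 0.4–0.6%, 38% at 10%. This says nothing about mild or average reflux, and is no argument for a larger trial.

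**What to change.** Keep n = 100.

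1. In {20a}, state that the ordered bile reflux grade (none, mild, average, severe) will be compared between arms with a Wilcoxon rank-sum test, or with a proportional-odds model if that assumption is tenable, in place of the unordered chi-square or Fisher test. Give an effect estimate with its confidence interval.
2. Report severe or intractable reflux in each arm as counts with exact confidence intervals.
3. In the Discussion, limit the expected bile reflux conclusion to graded reflux, and say that an absence of severe events will not be taken as evidence of prevention.

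The cost is in analysis and wording only: no extra patients, visits or procedures. The one downside is a slightly less favourable stated claim about intractable reflux.

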## Trial status

At the time of the initial manuscript submission, recruitment had started on March 29, 2021, and the last patient is expected to be included in the study in December 2021. The study will be completed on April 5, 2024.

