**Discussion:**

With its 3-year follow-up time, this RCT will provide important data on the impact of wrapping the fundus of the excluded part of the stomach to prevent weight regain and biliary reflux after LOAGB.

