### Outcomes {12}

#### Primary outcome measure

Change of body mass index: The measure assesses a change of body mass index. Weight (kg) and height (cm) will be combined with the body mass index (BMI) kg/m^2^. Time frame: Baseline at 12, 24, and 36 months after surgery. Ideal body weight was calculated as 25 × [patient’s height in meters]^2^. Effectiveness endpoint follow-up included body mass index (BMI, kg/m^2^), change in BMI (ΔBMI [initial BMI − postoperative BMI]), excess BMI loss (EBMIL, % [(ΔBMI/initial BMI − 25) × 100]), and total weight loss (TWL, % [initial weight − postoperative weight/initial weight × 100]).

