#### Participant timeline {13}

The flow diagram of the study design is shown in Table 1.

**Table 1 Tab1:** The schedule of enrollment, interventions, and assessments of the FundoRingMGB trial

	Study period					
	Enrollment	Allocation	Post-allocation			Close-out
**Timepoint**	**V1 (preoperative)**	**V2 (operation)** ***March–December 2021***	**V3 12 months**	**V4 24 months**	**V5 36 months**	**April 2024**

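### The stated completion date of 5 April 2024 fits the first patient's 36-month visit, but the last patient's falls in December 2024, so most patients cannot have 36-month data at the planned close-out

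*Protocol article*

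**What the plan says.** Four parts of the protocol article bear on this.

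- **Trial status** gives the accrual period: "recruitment had started on March 29, 2021, and the last patient is expected to be included in the study in December 2021". It then fixes the end of the trial: "The study will be completed on April 5, 2024".
- **Participant timeline {13}, Table 1** places the operation visit in "March–December 2021". Follow-up visits are at 12, 24 and 36 months. The close-out column is headed April 2024, and the statistical analysis is marked in that column.
- **Outcomes {12}** counts the primary outcome from surgery: "Baseline at 12, 24, and 36 months after surgery". Bile reflux has the same three time points, and Table 1 also lists GERD symptoms at 36 months.
- **The Discussion paragraph of the abstract** presents the length of follow-up as the trial's contribution: "With its 3-year follow-up time, this RCT will provide important data".

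The planned size is 100 patients, 50 per group (Recruitment {15}).

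**The concern.** The final time point is defined per patient, from that patient's own operation. Operations are spread over about nine months, so the 36-month visits are spread over the same nine months three years later. A single close-out date can serve all patients only if it falls after the last of those visits. The stated date falls close to the first of them.

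The last of the three time points for the primary outcome is at stake, together with the 36-month results for bile reflux and GERD and the 3-year follow-up that the abstract promises. If the dates were followed, the 36-month comparison would contain only those patients whose operation came early enough in 2021. The intention-to-treat statement in the section on nonadherence and missing data does not help, because it cannot supply outcomes that have not yet been observed.

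**Working it through.** **Inputs from the protocol article**

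- First inclusion: 29 March 2021 (Trial status).
- Last inclusion: December 2021, day not given, so 1 and 31 December are both used (Trial status; Table 1).
- Completion: 5 April 2024 (Trial status). Close-out and analysis: April 2024 (Table 1), so 30 April 2024 is used as the generous reading.
- Last assessment: 36 months after surgery (Outcomes {12}; Table 1).
- Sample: 100 patients (Recruitment {15}).

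**Assumptions, because the article does not state them**

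- Operations are spread evenly over the calendar days of the accrual period.
- Each operation falls on the day of inclusion. Any delay between the two would make the shortfall larger.
- No early-visit allowance applies. This is varied in step 5.

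**Step 1. Where the stated date comes from.** First inclusion + 36 months = 29 March 2024. The stated completion date is 7 days later. Last inclusion + 36 months = 1 to 31 December 2024. The stated date therefore matches the first patient's last visit and not the last patient's.

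**Step 2. Shortfall for the last patient.** From 5 April 2024 to 1 December 2024 is 240 days, and to 31 December 2024 is 270 days. That is about 8 to 9 months. This step needs no accrual assumption.

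**Step 3. Share of patients with a true 36-month visit at close-out.** Share = (operation days up to close-out minus 36 months) / (all operation days), counting both end days.

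All operation days: 29 March to 1 December 2021 = 248; 29 March to 31 December 2021 = 278.

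| Close-out read as | Operated on by | Days | Share, accrual to 31 Dec | Share, accrual to 1 Dec |
|---|---|---|---|---|
| 5 April 2024 | 5 April 2021 | 8 | 8/278 = 2.9% | 8/248 = 3.2% |
| 30 April 2024 | 30 April 2021 | 33 | 33/278 = 11.9% | 33/248 = 13.3% |

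Of 100 patients this is about 3, or about 12 to 13.

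**Step 4. Follow-up at 5 April 2024.** The first patient would have just over 36 months. A patient operated on between 1 and 31 December 2021 would have 28.1 to 27.1 months. The range is therefore about 27 to 36 months. The last 24-month visit falls in December 2023, so the 12- and 24-month visits are due for every patient before completion.

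**Step 5. Sensitivity to an early-visit allowance of w days** (the article states none). Share by 5 April 2024 = (8 + w) / all operation days.

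- w = 30: 38/278 to 38/248 = 13.7% to 15.3%
- w = 60: 68/278 to 68/248 = 24.5% to 27.4%
- w = 90: 98/278 to 98/248 = 35.3% to 39.5%

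**Step 6. How uneven accrual would have to be.** For half the sample to reach 36 months by 5 April 2024, 50 operations would have to fall in the first 8 days: 50/8 = 6.25 per day, by the one surgeon named in Study setting {9}. On the 30 April reading it would be 50 operations in 33 days: 50/33 = 1.5 per day. That rate is not impossible, but half the patients would then be treated in the first 33 of 248 to 278 days.

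**The case against.** The best defence is that the completion date is an administrative slip. Visits are defined from each patient's surgery, audits are also planned to 36 months after surgery, and the date looks like a projection from the first patient. On that reading nobody intends to analyse 36 months on a few patients. The 12- and 24-month results are unaffected, and none of the three time points is singled out as the one that decides the trial. The December 2021 end of recruitment is itself only an expectation.

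Much of this stands. The article does not show an intention to run a truncated 36-month analysis, and the damage is confined to the last time point. The slip still needs correcting: Table 1 ties the statistical analysis to the same month, so the date governs which data the analysis holds, and it appears in two places. No section extends follow-up past it or limits the 36-month analysis to a subset.

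Some stronger readings are tempting but not supported:

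- A reader might infer as fact that almost no 36-month data would exist. The figure of about 3% depends on even accrual, a hard stop on 5 April and no visit window, none of which the article states. The other readings give more.
- A reader might infer that the few complete patients would be biased as the surgeon's early cases. The article documents no learning curve, and early cases are randomised to both arms.
- A reader might infer that the loss is worse because weight regain appears late. The background gives the typical size of regain and not its timing.
- A reader might infer that visits will be brought forward and labelled as 36 months. Nothing in the article says so.

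**Conclusion.** The dates contradict each other as written. That part rests on the article's own dates alone: a patient included in December 2021 cannot have a 36-month assessment before December 2024, 240 to 270 days after the stated completion.

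How many patients are affected depends on accrual. Under even accrual, about 97 of 100 would lack a true 36-month visit on 5 April 2024, and about 87 to 88 of 100 on 30 April 2024. Even a 90-day early-visit allowance before 5 April leaves 60% or more without one. Only heavily front-loaded accrual would change the conclusion that most patients are affected, and the article's expectation of inclusion up to December does not suggest it.

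The 36-month comparison and the 3-year follow-up claim therefore cannot be delivered for most of the sample on the stated timetable. The comparisons at 12 and 24 months are not affected by it. This is an internal inconsistency in the timetable and not a fault in the choice of endpoint or length of follow-up.

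**What to change.** Move the completion date in Trial status and the close-out heading in Table 1 to after the last patient's 36-month visit, which means December 2024 or later if the last operation is in December 2021. Add one sentence saying that the final 36-month analysis is not run before that visit has taken place.

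The cost is a protocol amendment to two dates and a final analysis about 8 to 9 months later. The visits concerned are already planned, so no extra patients or procedures are needed. Whether the trial registration carries the same date cannot be seen from the article; the sponsor should check it at the same time.
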